## Abstract

**Background:**

Indigenous Australians experience an overwhelming burden of chronic disease, including cardiovascular diseases. Periodontal disease (inflammation of the tissues surrounding teeth) is also widespread, and may contribute to the risk of cardiovascular diseases via pathogenic inflammatory pathways. This study will assess measures of vascular health and inflammation in Indigenous Australian adults with periodontal disease, and determine if intensive periodontal therapy improves these measures over a 12 month follow-up. The aims of the study are: (i) to determine whether there is a dose response relationship between extent and severity of periodontal disease and measures of vascular health and inflammation among Indigenous Australian adults with moderate to severe periodontal disease; and (ii) to determine the effects of periodontal treatment on changes in measures of vascular health and inflammation in a cohort of Indigenous Australians.

**Methods/Design:**

This study will be a randomised, controlled trial, with predominantly blinded assessment of outcome measures and blinded statistical analysis. All participants will receive the periodontal intervention benefits (with the intervention delayed 12 months in participants who are randomised to the control arm). Participants will be Indigenous adults aged ≥25 years from urban centres within the Top End of the Northern Territory, Australia. Participants assessed to have moderate or severe periodontal disease will be randomised to the study's intervention or control arm. The intervention involves intensive removal of subgingival and supragingival calculus and plaque biofilm by scaling and root-planing. Study visits at baseline, 3 and 12 months, will incorporate questionnaires, non-fasting blood and urine samples, body measurements, blood pressure, periodontal assessment and non-invasive measures of vascular health (pulse wave velocity and carotid intima-media thickness). Primary outcome measures are pulse wave velocity and carotid intima-media thickness.

**Discussion:**

The study will assess the periodontal-cardiovascular disease relationship among Indigenous Australian adults with periodontal disease, and the effectiveness of an intervention aimed at improving periodontal and cardiovascular health. Efforts to understand and improve Indigenous oral health and cardiovascular risk may serve as an important means of reducing the gap between Indigenous and non-Indigenous health in Australia.

**Trial Registration:**

Australia and New Zealand Clinical Trials Register (ANZCTR): ACTRN12610000817044

## Background

### The health of Indigenous Australians

Indigenous Australians are disadvantaged on almost every health and social indicator relative to their non-Indigenous counterparts. They have 15-20 years shorter life expectancy, much higher levels of cardiovascular disease, diabetes and other chronic conditions including poor oral health status, and are more likely to experience disability and reduced quality of life due to ill health [1-4]. They also have a high burden of infectious diseases alongside significant rates of metabolic risk [5].

### Cardiovascular disease

Cardiovascular diseases are a leading cause of morbidity and mortality in developed countries. The disease process that underlies the majority of cardiovascular events is atherosclerosis, an inflammatory disease of the blood vessel wall. The earliest physical evidence of atherosclerosis are fatty streaks, which are typically present in childhood. In the presence of arterial endothelial dysfunction, which is involved in the initiation and progression of atherosclerosis, these early lesions progress through to complex atheromatous lesions in adulthood, finally resulting in occlusion, plaque rupture and ischaemic events [6].

### Periodontal disease

Periodontal disease is inflammation of the tissues surrounding teeth and results from a complex interplay between bacteria and host risk factors such as long-term smoking, poor oral hygiene, poorly controlled diabetes, stress and genetic predisposition [7]. Not only have periodontal organisms adapted to survive within an environment that is constantly besieged by host defences, but they flourish in the presence of inflammation, enabling their capacity to invade host tissues and gain direct access to the circulation [8]. Repeated bacteremias and endotoxemias are characteristic of periodontal infection, and periodontal organisms have been found to co-localise within atheromatous plaques [9]. The constant exposure of the vasculature to these pathogens provides an opportunity for endothelial inflammatory activation and functional impairment. Clinically, periodontal disease manifests as deepening of the epithelial attachment around teeth, loss of periodontal attachment and, ultimately, tooth loosening.

Periodontal disease is widespread and poses a substantial problem among Australian Aboriginal populations. In Australia's second National Survey of Adult Oral Health (NSAOH), mild forms of periodontal disease were reported to affect 20 percent of the adult population, while more severe forms affected about 1 in 40 adults [10], increasing to 3 in 10 adults when the Indigenous population were considered in isolation. Similarly, Endean and colleagues reported that among Aboriginal adults seeking dental care in several Central Australian remote communities, 30.2 percent had a history of this condition [11]. The prevalence of tooth loss due to periodontal disease among Aboriginal populations is also high [12].

Periodontal disease has been associated with atherosclerosis [13], cardiovascular disease [14], diabetes [15], pre-term low birth weight [16], stroke [17], and premature death [18]. Accordingly, periodontal disease may account for a portion of the risk for cardiovascular disease via a shared pathogenic underlying inflammatory response (figure 1)[8].

**Figure 1 F1:**
[figure not shown]
**Conceptual model of periodontal disease and cardiovascular surrogate endpoint response**.

### Periodontal therapy decreases systemic inflammation and improves endothelial function

Treating periodontal disease results in a functional improvement in cardiovascular status [19-22]. These studies are consistent with the concept that periodontal disease may be an important source of infectious and inflammatory vascular stress, and that periodontal therapy may be of particular clinical relevance in populations with high prevalence of both periodontal disease and cardiovascular disease.

### Aims & hypotheses

The PerioCardio study will assess measures of vascular health and inflammation in Indigenous Australian adults with periodontal disease, and determine if intensive periodontal therapy improves these measures over a 12 month follow-up. The specific aims and hypotheses are:

Aim 1: To describe the extent and severity of measures of vascular health and inflammation in Indigenous Australian adults with moderate or severe periodontal disease.

Hypothesis: The extent and severity of cardiovascular surrogate endpoints in an Indigenous population with periodontal disease will be high.

Aim 2: To determine whether there is a dose-response relationship between extent and severity of periodontal disease and measures of vascular health and inflammation among Indigenous Australian adults.

Hypothesis: The extent and severity of periodontal disease has a dose-response relationship with vascular health and inflammatory measures.

Aim 3: To determine whether periodontal treatment influences vascular health and inflammation in Indigenous Australians with moderate to severe periodontal disease.

Hypothesis: Periodontal therapy will improve vascular health and inflammatory markers in Indigenous Australians.

## Methods/design

### Study design and overview

This will be a randomised, controlled trial, with predominantly blinded measurement of cardiovascular endpoints, and blinded statistical analysis. All participants will receive, or be offered, the periodontal intervention benefits. A schema outlining the study design is presented in Figure 2. The PerioCardio study has been registered with an international clinical trials registry (ANZCTR; ACTRN12610000817044), and will be reported as per the CONSORT statement. Recruitment for the study commenced in June 2010.

**Figure 2 F2:**
[figure not shown]
**Study plan schema**.

### Setting & location

Participants will be recruited from urban centres within the Top End of the Northern Territory, Australia, facilitated through the following Aboriginal Medical Services or health facilities: Danila Dilba Health Services (Darwin and Palmerston), Bagot Community Health Centre (Darwin), Royal Darwin Hospital, Darwin Dental Centre (Northern Territory Oral Health Services, Department of Health), Northern Territory Correctional Services (Darwin), and Wurli Wurlinjang (Katherine).

### Participants and recruitment

Participants will be Indigenous Australians aged ≥25 years that have lived in their current location for ≥2 years and who plan to live at their current location for the next 2 years. Those participants who have moderate or severe periodontal disease will be randomised to the intervention or control arm of the study. Those participants without periodontal disease, or only mild periodontal disease, will not be included in the trial. Baseline questionnaires will, however, be assessed in these participants in order to study the social, demographic, lifestyle and general health correlates of periodontal disease in Indigenous Australians.

Exclusion criteria include: a history of rheumatic heart disease, prior myocardial infarction, stroke or coronary revascularisation, other cardiac conditions requiring antibiotic prophylaxis for prevention of subacute bacterial endocarditis, obvious endodontic lesions, other sources of oral infection, treatment for periodontal disease within the previous six months.

Feedback to participants will be provided at the end of each examination. Participants with unexpected abnormal results will be referred to an appropriate health care provider. In addition, written results will be provided in a plain language and culturally appropriate manner to individual participants and to their nominated primary health care provider. Whenever possible, participants with abnormal results will be contacted by telephone or in person. The results packet will then be mailed or hand-delivered, as appropriate. A $50 gift voucher to a local store will be provided to participants at the end of the examination or with their results as a gift of appreciation for their participation in the study.

### Ethics

The study was approved by the joint Menzies School of Health Research - Northern Territory Department of Health Human Research Ethics Committee. The project was considered and approved by both the Aboriginal sub-committee, which has absolute right of veto, and by the main committee. The study was also approved by the Central Australian Human Research Ethics Committee, Northern Territory Correctional Services Research Committee, University of Adelaide Human Research Ethics Committee, and the Aboriginal Health Council of South Australia.

### Consent

Potential participants are provided with written information about the study, face-to-face discussion with a staff member, and given an opportunity to ask questions. If required, an interpreter explains all information relating to the study. Those who indicate that they wish to participate are then asked to complete and sign a consent form. Consent is obtained using the NHMRC Guidelines for Ethical Conduct in Aboriginal and Torres Strait Islander Health Research. All participants are informed that their participation is voluntary and that they can refuse or withdraw from participating and need give no reason or justification for their decision and that it will not affect their medical or dental care. Participants are asked to provide separate consent for various elements of the study, including: vascular assessments, blood and urine samples, body measurements, blood pressure and questionnaires. They are also asked whether they want a report sent to their primary health care provider and whether their blood and urine samples can be stored at Menzies School of Health Research for 3 years.

### Screening for periodontal disease

Following confirmation of contact details and eligibility, and after obtaining informed consent, a participant will be screened for periodontal disease, using the US Centers for Disease Control and Prevention and the American Academy of Periodontology definitions [23]. Thus, a case of moderate periodontitis is considered as the presence of either two sites between adjacent teeth with ≥4 mm attachment loss or at least two such sites with ≥5 mm pockets, and severe periodontitis as having at least two sites between adjacent teeth with ≥6 mm attachment loss and at least one pocket ≥5 mm.

### Randomisation

After screening for periodontal disease, those with moderate or severe periodontal disease are randomised on a 1:1 basis to either the treatment or control group. A computer generated permuted block randomisation sequence is used, stratified by recruitment site (Darwin/Palmerston, Katherine).

### Intervention

Individuals randomised into the 'treatment group' undergo a periodontal intervention based on the technique described previously [20]. This involves intensive removal of subgingival and supragingival calculus and plaque biofilm by scaling and root-planing. Participants are offered local anaesthesia prior to the procedure. The procedures are carried out with the use of Hu Friedy hand scalers and a piezoelectric ultrasonic scaler with universal tips. Dental extraction of teeth that cannot be saved is not performed as part of the treatment protocol. The intervention is performed by two oral health practitioners who have received additional training with these techniques. The periodontal intervention occurs during a single untimed visit to the study clinic.

Oral hygiene instruction and an oral hygiene pack containing a toothbrush and tooth paste are provided to all participants at the baseline visit. Information concerning dental extractions during the course of the study is recorded.

### Participant involvement

Each participant randomised will attend the study clinic a total of 3 times (figure 2).

Periodontal treatment will be offered to those in the control group at 12 months post-randomisation, to ensure that all participants are able to receive the oral health benefits of the periodontal treatment. The periodontal treatment offered to participants in this study is beyond that which forms routine treatment within the government funded system. Participants are not restricted from seeking periodontal treatment during the study through the private health system.

### Data collection techniques

#### Dental assessment

including tooth presence, caries experience, periodontal destruction, gingivitis and calculus, plaque, oral mucosal lesions and trauma.

#### Clinical and anthropometric measures

Blood pressure is measured while seated using an automated device (Welch Allyn Medical Products, Skaneateles Falls, USA). Three measurements of systolic and diastolic pressure are made, with three minutes between readings. The mean values of the final two recordings will be used in statistical analysis.

Height is measured to the nearest 0.1 cm using a wall-mounted stadiometer.

Weight is measured to the nearest 0.1 kilogram, using a portable weight scale (Tanita HD-351, Arlington Heights, USA) with participants lightly clothed. Two separate measurements of weight are recorded and if they differ, then a third measurement of weight is taken.

Waist and hip circumference are measured to the nearest 0.1 centimetre using a 2-metre non-stretch flexible steel tape (Model W606PM Lufkin, USA), as previously described [24].

#### Common carotid intima-media thickness (IMT) and M-mode imaging

External ultrasound of the common carotid artery is performed with the patient lying in a supine position, neck slightly extended and the head tilted away from the side being scanned whilst connected to 3-lead ECG, to monitor cardiac cycle. Bilateral longitudinal images of the carotid bulb and common carotid artery, up to 15 mm proximal to the bulb, are obtained using a portable ultrasound (Sonosite MicroMaxx, Bothell, USA), with a 10-5 MHz linear array transducer. Loops are obtained of each artery, and stored in a digital format for batch analysis by an observer blinded to participant group, characteristics and study visit. Measurement of carotid IMT will be performed on the far wall of the common carotid artery at end diastole, within 10 mm proximal to the carotid bulb, on two consecutive cardiac cycles.

M-mode imaging of the arterial diameter during the cardiac cycle is used to assess regional stiffness of the common carotid artery. The area of interest for the stiffness measure is between 10 mm and 15 mm proximal to the bulb. Loops of each side are obtained, ensuring that both the near and far walls are clearly visible and the artery is perpendicular to the angle of insonation. Internal diameter of the artery during systole and end-diastole will be measured over three cardiac cycles to generate the following indices: pressure-strain elastic modulus, Young's modulus, cross-sectional compliance, distensibility coefficient.

#### Pulse wave velocity (PWV)

PWV is measured between the common carotid and dorsalis pedis arteries using applanation tonometry (SphygmoCor-PVMx device, AtCor Medical, Sydney, Australia), with participants in a supine position for at least 10 minutes prior to commencement of measures. The common carotid artery is located via lateral palpation along the thyroid cartilage while the dorsalis pedis artery is located between the first and second metatarsals on the dorsal surface of the foot. A pressure tonometer is placed transcutaneously above the corresponding artery to record the pulse pressure waveform while simultaneously recording the ECG signal, which provides an R-wave timing reference. The arteries are assessed consecutively. The resultant PWV score is calculated via computer algorithm as the mean time difference between the R-wave and the pressure wave per heart/pulse beat and the arterial path length between the two recording sites. To correct against measurement error, the distance from the common carotid location and the sternal notch will be subtracted from the distance between the sternal notch and the dorsalis pedis site. Data quality control for this measurement requires that standard deviation not exceed 10%. In the instances that this occurs, PWV will be remeasured. Measurement of PWV is undertaken automatically by the acquisition machine, and as such the observer will not be blinded to study participant characteristics.

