### Primary and secondary outcomes

The primary outcome measures for purposes of this investigation will be carotid IMT and PWV. Secondary outcome measures will include CRP, IL-6, ADMA, and HbA1c.

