### Data handling and statistical methods

At the time of baseline assessment, data is collected on paper forms and then entered into a Microsoft Access database. Data is stored securely at Menzies School of Health Research. In brief, the plan for the analysis is:

Aim 1: descriptive statistics including mean and standard deviation for normally distributed variables, geometric mean and 95% confidence interval for non-normally distributed data, and percentages for categorical variables.

Aim 2: associations of the extent and severity of periodontal disease with measures of vascular health and inflammation from cross-sectional analysis at baseline, using correlation analysis, and multivariable regression modelling adjusted for cardiovascular risk factors.

Aim 3: intention to treat analysis comparing cardiovascular surrogate endpoints between the two randomised groups. Primary outcomes are carotid IMT at 12-months and PWV at both 3- and 12-months. Correlations between the changes from baseline to 3- and 12-months in carotid IMT, PWV and secondary outcomes will be determined.

Appropriate transformation of the data will be performed as required. Crude correlations will be detailed, followed by multivariable modelling. Statistical significance will be inferred at 2*P *≤ 0.05.

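### The PWV observer is left unblinded because the device is automatic, yet acquisition depends on the operator and PWV supplies two of the three primary comparisons

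*Protocol article*

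**What the plan says.** All references are to the protocol article.

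- **Primary and secondary outcomes:** "The primary outcome measures for purposes of this investigation will be carotid IMT and PWV".
- **Data handling and statistical methods (Aim 3):** "Primary outcomes are carotid IMT at 12-months and PWV at both 3- and 12-months". That makes three primary comparisons, two of them PWV.
- **Pulse wave velocity (PWV):** the section ends with the blinding decision and its reason: "Measurement of PWV is undertaken automatically by the acquisition machine, and as such the observer will not be blinded to study participant characteristics". Earlier it describes how the value is obtained: "The common carotid artery is located via lateral palpation along the thyroid cartilage"; the foot artery is located on the dorsum of the foot; a tonometer is placed over each artery in turn; and the path length is the sternal-notch-to-foot distance minus the carotid-to-sternal-notch distance. On quality, "Data quality control for this measurement requires that standard deviation not exceed 10" percent, and a recording that fails is repeated.
- **Common carotid intima-media thickness (IMT) and M-mode imaging:** IMT loops are "stored in a digital format for batch analysis by an observer blinded to participant group, characteristics and study visit".
- **Study design and overview:** the trial is described as one "with predominantly blinded measurement of cardiovascular endpoints, and blinded statistical analysis".
- **Intervention** and **Participant involvement:** controls are offered treatment at 12 months. No sham procedure is described.

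**The concern.** The PWV section gives automatic acquisition as the reason for not blinding the observer. Automation of one step does not make the other steps objective, and it would not prevent the operator from being masked in any case. The protocol protects one primary outcome by a reader masked to group and gives the other no stated equivalent.

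Participants know whether they have had scaling and root-planing, and no sham is described, so masked assessment is the main protection left for a surrogate endpoint. If the person holding the tonometer knows the arm, a favourable PWV result at 3 or 12 months can be attributed to how the measurement was taken. The trial would then have little in its own protocol with which to answer.

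**Working it through.** **1. How much of the primary analysis is affected.** The comparisons are IMT at 12 months (masked reading), PWV at 3 months and PWV at 12 months (observer not blinded). PWV supplies 2 of 3.

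**2. Which steps are automatic.** Setting the PWV section's steps beside its stated reason:

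| Step described | Automatic? |
|---|---|
| Locating the carotid (palpation) and foot arteries | No |
| Placing the tonometer on each artery, one after the other | No |
| Surface distances that form the path length | No; someone has to measure them |
| Time difference between R-wave and pulse wave, and the final PWV | Yes, by algorithm |
| Repeating a recording that fails the quality limit | Numeric trigger, but a new operator-dependent acquisition |

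**3. How an acquisition difference reaches the outcome.** PWV = L / Δt, where L is the path length and Δt the transit time. At fixed Δt, a 1% change in L changes PWV by 1%. The Sample size section targets a 10% reduction, so each 1% of systematic between-arm difference in L is one tenth of the target. Error that is the same in both arms cancels from the comparison; only a difference by arm matters.

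**4. What the sample size implies about precision.** The Sample size section gives 144 evaluable participants, 0.80 power and a 10% PWV difference, with significance at 0.05 (two-sided in the analysis section). It gives no SD, so 144 cannot be reproduced independently. Solving for the SD with 72 per arm:

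- standardised difference = (1.960 + 0.842) × √(2/72) = 0.467
- implied SD = 10% / 0.467 = 21.4% of the mean
- check: an SD of 21.4% and a 10% difference return 72 per arm and power 0.80 (circular, but it confirms the algebra)
- SE of the difference = 21.4% × √(2/72) = 3.6% of the mean

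**5. Illustration of a bias.** If there is no true effect and the arms differ by a measurement bias b, the type I error of one two-sided comparison is Φ(b/SE − 1.96) + Φ(−b/SE − 1.96). The values of b are assumed; the SD rows of 15% and 25% show sensitivity around the implied value.

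| SD (% of mean) | SE | b = 1% | b = 2% | b = 3% | b = 5% |
|---|---|---|---|---|---|
| 15 (assumed) | 2.5% | 0.069 | 0.126 | 0.224 | 0.516 |
| 21.4 (implied) | 3.6% | 0.059 | 0.087 | 0.134 | 0.288 |
| 25 (assumed) | 4.2% | 0.057 | 0.077 | 0.111 | 0.224 |

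At the implied SD, a bias of 2–3% is 0.56–0.84 of a standard error.

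**The case against.** **Masking to group is not literally denied.** The PWV sentence speaks of participant characteristics, while the IMT section lists group, characteristics and visit as separate items. A reader might infer that the article declares the PWV operator unblinded to allocation. It does not. What stands is that nothing says the operator is masked to group, and an unmasked operator is the natural reading.

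**The gap is disclosed.** A reader might infer that "predominantly blinded measurement of cardiovascular endpoints" is untrue because two of three primary comparisons are not blinded. The documents do not support that. The phrase covers cardiovascular endpoints in general. Of the six named outcomes (IMT, PWV, CRP, IL-6, ADMA, HbA1c), PWV is the only one declared unblinded; four of the others are blood assays with no bedside operator. The phrase is a fair disclosure, but disclosing the gap does not close it.

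**The repeat rule is not evidence of bias.** It is tempting to set the 10% limit on the SD of a recording against the 10% effect sought. The first concerns the quality of a single measurement and the second a difference between arm means, so the match means nothing. A fixed numeric trigger also limits discretion, and nothing in the article suggests that repeats would differ by arm.

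**The bias sizes are assumed.** This stands. If the path is 1.0–1.4 m (an assumption; the article gives no length), 2–3% is about 2.0–4.2 cm of distance error, consistently in one direction by arm. Tape error alone may not reach that.

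**A journal article leaves staffing to the full protocol.** Who measures and in what order could well be there, and nothing says that the two treating practitioners take PWV. But this point does not rest on an omission: the article states a decision not to blind, with a reason that its own description undercuts.

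**Conclusion.** The concern holds as a design point. The stated reason does not justify leaving the PWV observer unmasked, and the protocol gives no alternative safeguard for two of its three primary comparisons. The exposure is confined to PWV. IMT is read by a masked observer, although the article does not say whether the person acquiring the images is masked.

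The documents support a risk of detection bias, not its size or direction. The rise from 0.05 to about 0.09–0.13 rests on an assumed 2–3% bias and on an SD back-calculated from the stated power; over SDs of 15–25% the same bias gives 0.08–0.22. The conclusion does not depend on those figures. It should be corrected, but it does not invalidate the trial, and if the operator is in practice masked to group, a sentence saying so largely resolves it.

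**What to change.** 1. Replace the last sentence of the PWV section with a statement that PWV at 3 and 12 months is taken by an existing team member who did not deliver the periodontal treatment and is not told the allocation, before that visit's periodontal examination. The small downside is a rostering constraint, likely greatest at the smaller site. Participants may still reveal their arm, so masking will not be perfect.
2. Name the M-mode carotid stiffness indices as a supportive secondary outcome, and state that they are read from stored loops by the blinded reader. The images are already collected, but the outcomes section does not list the indices, and blinded batch reading is spelled out only for the IMT loops. They measure regional rather than carotid-to-foot stiffness and their acquisition is still manual, so they support PWV and do not replace it. The cost is wording and some reading time.
3. Where masking cannot be achieved, report PWV explicitly as an unblinded primary outcome.

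Reusing each participant's baseline path length should not be made compulsory. Arteries are located afresh at each visit, so a carried-forward distance could mismatch the transit time, and the article does not say whether the baseline measurement precedes randomisation.

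Recruitment began in June 2010, so the change can apply only to visits still to come; the report should say from when it applied.
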